#### Secondary outcomes

Patients will be asked to complete a daily diary to evaluate the severity of the individual symptoms (abdominal pain, abdominal discomfort, bloating, flatulence, urgency, and mucus in the stool) and the severity of overall symptoms on a 100-mm visual analog scale (VAS) during run-in, administration, and follow-up periods [22]. The VAS scores are rounded to the nearest integer in millimeters. Patients will also be requested to fill in a daily diary to assess stool frequency and bowel functions on the basis of the consistency defined by the Bristol stool scale [21] and the ease of passage, as defined by the adjectival scale (from manual disimpaction to incontinence) [23].

A quality of life measurement for persons with irritable bowel syndrome (IBS-QoL) is a 34-item questionnaire assessing the degree to which IBS interferes with the patient's quality of life. The IBS-QoL is composed of 8 dimensions, including dysphoria, interference with activity, body image, health worry, food avoidance, social reaction, sex, and relationships. Each item is evaluated on a 5-point Likert scale with a higher score indicating a better quality of life [24]. The IBS-QoL will be filled out at the administration period baseline (week 0), the administration period end (week 8), and the end of the follow-up period (week 10).

#### Assessment of intestinal permeability

Intestinal permeability reflects the intactness of the intestinal mucosal barrier, which regulates the passive permeation of the luminal contents [25]. It is possible to assess intestinal permeability by evaluating the urinary excretion of lactulose and mannitol given orally [26]. Lactulose is only slightly absorbed and serves as a measure of the mucosal integrity while mannitol is easily absorbed and serves as a measure of the transcellular uptake [27]. The lactulose/mannitol (L/M) test is nontoxic and noninvasive in humans and is a stable measurement that is not affected by gastric emptying, intestinal motility, and renal function [28]. Therefore, the L/M test is a relevant method to measure intestinal permeability in the current trial. An increased ratio of the excretion of lactulose to mannitol suggests increased intestinal permeability [26]. Increased intestinal permeability is reported in various intestinal diseases associated with diarrhea such as leaky gut syndrome [25] or IBS [29,30].

The evaluation procedure is as follows: after an overnight fast, each subject will void to empty his or her bladder and then ingest 13.9 g of lactulose together with 5.3 g of mannitol dissolved in 500 mL of water. Urine will be collected over the next 8 h in plastic bags. Patients will drink approximately 2 L of water during the test, and other foods or liquid will not be allowed. The entire urine volume will be measured for 8 h and a 45-mL urine sample will be stored at -70°C until assayed. The urine will be collected at the baseline (week 0) and at the end of the administration (week 8) period.

#### Pattern analysis of intestinal microbiota

Associations have been observed between IBS patients' symptoms and the presence or quantities of certain gastrointestinal bacteria [31]. In the current study, we will focus on the change in the composition of the intestinal microbiota after administration of the study agents. Each subject will be expected to submit 5 g of fecal samples for bacteriological studies at the baseline (week 0) and at the end of the administration (week 8) periods. The samples will be collected immediately before urine collection and stored at -70°C prior to analysis. The fecal samples will be analyzed in a qualified laboratory (Cell Biotech Co., Ltd., Seoul, Korea) by the denaturing gradient gel electrophoresis (DGGE) method and real-time polymerase chain reaction (RT-PCR), which is a useful genotypic technique for detecting changes in the microbiota [32].

### Quality control

To maintain the accuracy and quality of the clinical trial, audits and monitoring will be implemented by the Marinet Corporation, a CRO located in Seoul, Korea. Clinical research associates will regularly monitor whether the clinical trial is proceeding based on the protocol by checking trial master files, informed consent forms, case report forms, adverse events, and compliance with study agents.

### Statistical analysis

Statistical analysis of all data will be performed by a specialized statistician in a blind manner. To assess the efficacy of this trial, both the *intention-to-treat *and *per-protocol *populations will be analyzed. Baseline characteristics will be compared by Pearson's chi-square test and analysis of variance (ANOVA). The target variables for analysis in this study include the following: (1) AR and proportion of responders (primary outcomes); (2) VAS for abdominal pain and diarrhea; (3) bowel function scores (frequency, consistency, and ease of passage); (4) severity of individual symptoms (abdominal pain, abdominal discomfort, bloating, flatulence, urgency, and mucus in the stool) and overall symptoms; and (5) IBS-Qol. All values will be presented as mean ± SEM. Comparison between the 4 groups will be performed on the basis of repeated measure ANOVA, and the paired *t*-test will be used to compare between the baseline and after a certain period in each group. The analysis for characteristics such as gender and age between groups will be conducted along with Pearson's chi-square test. All statistical analyses of the data will be performed using the SPSS program, version 16.0 (SPSS Inc., Chicago, IL) and a *P *value < 0.05 will be considered statistically significant.

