## Materials and methods

### Objectives

The aims of the study are as follows: (1) to verify the effect of GJS combined with Duolac7S on D-IBS; and (2) to analyze mechanisms and establish scientific evidence for the use of GJS with Duolac7S by investigating changes in intestinal permeability and the composition of intestinal microbiota.

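### The analysis list names a VAS for diarrhea that the diary, as described, does not record; the two sections need to be reconciled

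*Protocol article*

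**What the plan says.** Only the protocol article is at hand. Three of its parts bear on this point.

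- **Secondary outcomes, VAS items.** On a 100-mm VAS, the daily diary rates the "severity of the individual symptoms (abdominal pain, abdominal discomfort, bloating, flatulence, urgency, and mucus in the stool". A further scale of the same kind is kept for how severe the symptoms are as a whole. That makes six symptom scales and one overall scale.
- **Secondary outcomes, bowel function.** Patients also keep a "daily diary to assess stool frequency and bowel functions on the basis of the consistency defined by the Bristol stool scale", together with ease of passage on an adjectival scale. None of these is a VAS.
- **Statistical analysis.** The list opens with "The target variables for analysis in this study include the following" and has five items. Item (1) is adequate relief and the proportion of responders. Items (2) and (3) read "2) VAS for abdominal pain and diarrhea; (3) bowel function scores (frequency, consistency, and ease of passage". The list ends with "4) severity of individual symptoms (abdominal pain, abdominal discomfort, bloating, flatulence, urgency, and mucus in the stool) and overall symptoms; and (5) IBS-Qol".

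The second aim, under Objectives, is to study mechanism by "investigating changes in intestinal permeability and the composition of intestinal microbiota". The second hypothesis predicts lower permeability and a changed proportion of lactic acid bacteria after 8 weeks. The Abstract names both measures as secondary outcomes, and urine and feces are collected at weeks 0 and 8.

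**The concern.** Two explicit lists in the same article disagree. The analysis list contains a diarrhea VAS, and the description of the diary contains none. This is not detail left to a later document, because no analysis plan can analyse a scale that was never recorded.

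The trial enrols diarrhea-predominant patients, so a reader of the results will look for the variable labelled diarrhea. If it has no source, someone must later decide what it meant. Stool frequency, Bristol consistency and urgency are all candidates, and they need not agree, least of all with about 15 patients per arm. It is better to settle the meaning in advance.

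A lesser concern is that the list goes down to ease of passage and mucus in the stool, yet does not name the two biological outcomes on which the second aim rests.

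**Working it through.** The point depends on no sample size, power or alpha, so the check sets the sections side by side.

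**Step 1. VAS items recorded against VAS items listed for analysis**

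| VAS item | Recorded (Secondary outcomes) | Listed (Statistical analysis) |
|---|---|---|
| Abdominal pain | yes | items (2) and (4) |
| Abdominal discomfort | yes | item (4) |
| Bloating | yes | item (4) |
| Flatulence | yes | item (4) |
| Urgency | yes | item (4) |
| Mucus | yes | item (4) |
| Overall severity | yes | item (4) |
| Diarrhea | **no** | item (2) |

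Recorded: 6 + 1 = 7 scales. All seven are covered by item (4). Item (2) therefore adds one repeat (pain) and one scale with no described source (diarrhea).

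**Step 2. Could item (2) be shorthand for something recorded elsewhere?** Stool frequency, consistency and ease of passage are on other scales and already form item (3), so item (2) is not another name for them. The Abstract speaks only of a VAS for IBS symptoms in general, which does not supply a diarrhea scale. No other section describes one.

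**Step 3. Does diarrhea have any usable analysis variable?** Yes. Stool frequency and Bristol consistency are recorded daily and listed in item (3). The urgency VAS is in item (4).

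**Step 4. Declared secondary outcomes against the list**

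| Secondary outcome family (Abstract) | In the five-item list |
|---|---|
| VAS for symptoms | yes, items (2) and (4) |
| Quality of life | yes, item (5) |
| Intestinal permeability | not named |
| Intestinal microbiota | not named |

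Two of the four families are not named. The opening words of the list do not claim completeness, however. The section begins by speaking of all data, and the sentence on the four-group repeated measures ANOVA is not limited to the five items.

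**The case against.** The strongest case on the other side is that this is a slip of wording in a secondary variable, in an article that condenses a fuller protocol. Much of that stands.

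- A reader might infer that diarrhea cannot be analysed and that a substitute is bound to be picked after the data are seen. The documents do not support this. Item (3) already lists collectable measures of diarrhea, and the analysis is to be done blind.
- A reader might infer that the second aim has no planned between-arm comparison. The documents do not support this either. The list is not exhaustive, the four-group comparison is stated generally, and values at weeks 0 and 8 fit it. Further detail may stand in the full protocol or analysis plan.
- A reader might take the repeat of abdominal pain, or the place of item (2) directly after the primary outcomes, as giving it extra weight. The section states no hierarchy among items (2) to (5), and nothing in it counts items, so the repeat changes no result.
- A reader might conclude that the diary certainly lacks the scale. The diary form is not shown, so the error could lie in either section.

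The mismatch itself is left standing: as the article describes the diary, the diarrhea VAS of item (2) has no source.

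**Conclusion.** The point holds as an internal contradiction between Secondary outcomes and Statistical analysis. One of the five target variables is affected: half of it has no described source and the other half repeats item (4). The consequence is limited to secondary symptom reporting. The primary outcomes and the sample size statement are untouched.

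That permeability and microbiota are not named is a secondary point. It is a reason to complete the list, not evidence of a missing analysis.

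The conclusion assumes that the Secondary outcomes section describes all the diary's VAS items. If the diary form does carry a diarrhea VAS, the fault moves to that section and the correction changes accordingly.

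**What to change.** Check the diary form and reconcile the two sections before analysis.

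- **If the diary has no diarrhea VAS:** delete item (2). Keep abdominal pain and overall severity once each, under item (4). State under item (3) that diarrhea is assessed from stool frequency and from the weekly share of loose or watery stools on the Bristol scale.
- **If the diary has one:** add it to the VAS items in Secondary outcomes, and list abdominal pain only once in the analysis section.

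Overall severity should not be moved into item (2) while it stays in item (4), as that would only create a new repeat.

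For the second aim, name the lactulose/mannitol ratio and the share of lactic acid bacteria in the list. Compare their week 8 values between arms with the week 0 value as covariate. With only two time points this answers the between-arm question directly, which paired *t*-tests within each arm do not. The group main effect of a repeated measures ANOVA also averages in the week 0 value, taken before any treatment effect could arise.

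The cost is wording in one or two sections. All the data named here are already collected, so no visit, patient or assay is added. The Trial status section says that recruitment is ongoing, so the change can be made before analysis.

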### Outcome measurements

#### Primary outcomes

Adequate relief (AR) will be used as a primary outcome to evaluate IBS symptom improvement. Patients are expected to report on a weekly basis their response to the following question: "In the past 7 days, have you had adequate relief of your IBS pain and discomfort?" AR will be measured at the end of each week during run-in, administration, and follow-up periods. Responders will be defined as patients reporting AR for at least 50% of the study weeks, which was applied as a major variable in previous studies [20,22]. The proportion of responders, another primary outcome, will be assessed individually during run-in, administration, and follow-up periods.

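### The methods stated for all outcomes (mean ± SEM, repeated-measures ANOVA, paired t-test) do not suit the two dichotomous primary outcomes, and no categorical method is assigned to them

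*Protocol article*

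**What the plan says.** The protocol article, Primary outcomes, defines two outcomes.

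- **Weekly adequate relief (AR).** The patient is asked "In the past 7 days, have you had adequate relief of your IBS pain and discomfort", and "AR will be measured at the end of each week during run-in, administration, and follow-up periods".
- **Responder status.** "Responders will be defined as patients reporting AR for at least 50% of the study weeks", and the proportion of responders "will be assessed individually during run-in, administration, and follow-up periods".

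The response options are not printed. That the answer is yes or no is inferred from the form of the question and from the responder rule, which counts weeks with relief.

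The Statistical analysis section lists "1) AR and proportion of responders (primary outcomes" as the first target variable, ahead of the VAS, bowel function, symptom severity and IBS-QoL. It then sets the methods without exempting any of them: "All values will be presented as mean ± SEM. Comparison between the 4 groups will be performed on the basis of repeated measure ANOVA". Within-group change from baseline goes to the paired t-test. Pearson's chi-square appears twice in that section, both times for patient characteristics and never for an outcome.

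**The concern.** The section does more than leave the primary method open. It prescribes one set of methods, and that set is made for continuous measurements. An analysis plan would have to depart from this text to analyse the primary outcomes suitably.

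Three things are at stake:

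- whether the responder comparison in the treated period has an applicable test at all;
- whether the printed error bars mean anything for proportions in arms of 12 to 15;
- whether the repeated-measures P-values on weekly relief hold their level.

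The article calls the trial a pilot (Sample size calculation; Discussion) that is meant to provide basic clinical data. Interpretable response rates and differences with honest uncertainty are therefore its main product.

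**Working it through.** **1. Group sizes.** Sample size calculation gives 12 completers per group and 20% drop-out. 12 / (1 − 0.20) = 15 per group, and 15 × 4 = 60, which reproduces the stated total. The checks below use n = 12 and n = 15.

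**2. Data structure.** Design gives 2 run-in, 8 administration and 2 follow-up weeks.

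| Outcome | Values per patient | Stated between-group method |
|---|---|---|
| Weekly AR | 8 binary values in the administration period, 12 in all | repeated-measures ANOVA |
| Responder, administration period | 1 binary value | repeated-measures ANOVA, but nothing is repeated |
| Responder, all three periods | 3 binary values | repeated-measures ANOVA possible, but it does not give the separate assessment by period that Primary outcomes describes |

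**3. SEM for a proportion.** For k responders out of n, coded 0/1, with p = k/n, SEM = √[p(1 − p)/(n − 1)].

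- k = 0: SEM = 0 for any n. The exact (Clopper–Pearson) upper 95% limit is 1 − 0.025^(1/n), which is 26.5% for n = 12 and 21.8% for n = 15.
- Exact binomial coverage of p ± 1.96 SEM, the interval a reader would build from the printed values:

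| True rate | n = 12 | n = 15 |
|---|---|---|
| 5% | 46% | 54% |
| 10% | 71% | 79% |
| 20% | 91% | 82% |
| 30% | 91% | 95% |
| 50% | 96% | 88% |

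The cause at low rates is the zero-width interval: at a true rate of 5%, the chance of no responder in an arm is 0.95^12 = 54% or 0.95^15 = 46%. By symmetry the same holds at 90% and 95%.

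**4. Size of the repeated-measures tests.** Null trials were simulated with four arms, n = 12 or 15, and weekly binary AR cut from a first-order autoregressive normal variable. The rates (flat 40%, or rising from 10% to 50% over treatment) and the correlations are assumptions; the article gives none. There were 6,000 trials per setting. Entries are the range over settings, at nominal 5%.

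| Weeks | Latent correlation | Group × time, uncorrected | Group × time, Greenhouse–Geisser |
|---|---|---|---|
| 8 | 0.5 | 5.8–6.7% | 4.2–4.4% |
| 8 | 0.8 | 7.3–7.9% | 3.9–4.7% |
| 8 | 0.9 | 7.9–9.1% | 4.3–5.0% |
| 12 | 0.5 | 6.3–7.5% | 3.9–4.1% |
| 12 | 0.8 | 8.6–9.5% | 4.0–4.6% |
| 12 | 0.9 | 10.1–10.8% | 4.1–5.0% |

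The group main effect rejected in 4.5–5.7% of trials across these settings.

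**5. Source of the inflation.** In separate runs with 15 per arm, continuous data with the same latent correlation were inflated more: 11.0% against 7.2% for binary (8 weeks, correlation 0.8), and 15.9% against 10.6% (12 weeks, correlation 0.9). The correction brought all four to between 4.2% and 5.2%. The cause is therefore uncorrected non-sphericity, not the yes/no scale.

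**6. One responder value per patient.** A one-way ANOVA of a single 0/1 value had almost the same size as chi-square (both 3.5–5.5%) at rates of 10–40%.

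**The case against.** The best defence is that ANOVA on 0/1 data is more robust than its assumptions suggest. Steps 4 and 6 support this: the group main effect keeps its level, and a one-way ANOVA of responder status behaves like chi-square. The article does not say that the group-by-time test will go uncorrected, and a sphericity correction is a detail commonly left to an analysis plan. The inflation is therefore conditional. At response rates of 20–50%, which may well apply during treatment, SEM-based coverage is a more tolerable 82–96%. All of this stands.

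A reader might draw four stronger conclusions, and the documents do not support them.

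- *That the primary tests are invalid.* Only one test is inflated, only without correction, and not because the data are binary.
- *That the error bars run past 0% or 100%.* The plan promises ± 1 SEM. At k = n − 1 the SEM is 1/n, so mean + SEM is exactly 100%, and by symmetry the bar never falls below 0%. Only wider intervals that the plan does not mention would cross.
- *That no risk difference is obtainable.* The mean of a 0/1 variable is the proportion, and a difference of means is a risk difference. What is lacking is a suitable interval, and an odds ratio.
- *That the effect is diluted to 8/12 = 67%.* This would need all 12 diary weeks to be pooled. The article does not say so, and for responders it calls for assessment by period.

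The defence does not remove the mismatch. The methods are stated for every value, the categorical test is confined to characteristics, and one responder value per patient cannot enter a repeated-measures comparison.

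**Conclusion.** The point holds as a mismatch between stated method and primary data. Its size:

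- the administration-period responder comparison has no applicable named test;
- the SEM is uninformative at 0% or 100%, and 95% intervals based on it cover 46–54% at a true rate of 5% and 71–79% at 10%;
- the group-by-time test on weekly relief, if uncorrected, has a true level of roughly 8–9% over 8 weeks or 11% over 12 weeks under strong serial correlation.

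This rests on three assumptions: that AR is answered yes or no; that extreme rates occur, which is plausible in the untreated run-in but not documented; and the simulated rates and correlations. The documents do not support calling the primary tests invalid. Whether to show SD or SEM, or which model to use, for the continuous secondary outcomes is a matter of preference and no part of this point.

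**What to change.** In Statistical analysis, separate the primary outcomes from the sentence that covers all values, and state:

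- **Responders, administration period:** Fisher's exact test for single contrasts, or logistic regression with the two treatment factors (GJS and Duolac7S). Report n/N (%) and the risk difference with a Newcombe or exact 95% CI.
- **Weekly relief, weeks 1–8:** GEE or a mixed model with logit link, with a small-sample correction of the standard errors because there are only 12 to 15 patients per arm.
- **Within-group change in a binary outcome:** McNemar's test in place of the paired t-test.
- **ANOVA, t-tests and mean-based summaries:** limit these to the continuous secondary outcomes.

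The cost is a few sentences and a little programming. Sample size, visits and data collection do not change. Recruitment was under way when the article was written (Trial status), so the change should be made and dated before unblinding.

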### Hypothesis

We hypothesize the following possibilities: (1) GJS combined with Duolac7S will show more beneficial effects on D-IBS symptoms than either GJS or Duolac7S alone; and (2) after 8 weeks of administration of GJS with Duolac7S, intestinal permeability will be lowered and the proportion of lactic acid bacteria in the intestine will be changed.

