### Design

The current study will be conducted as a placebo-controlled and double-blind trial with 60 patients being randomly allocated to 4 arms. The trial will be implemented at Kyung Hee University Hospital at Gangdong in Seoul, Korea.

Participants will be required to pursue a 2-week run-in (weeks -2 to 0), 8-week administration (weeks 0 to 8), and a 2-week follow-up period (weeks 8 to 10) and to record daily symptoms in a diary.

During the administration period, 1 pack 3 times a day (2 h after each meal) of GJS or its placebo and 1 capsule 2 times a day (2 h after breakfast and dinner) of Duolac7S or its placebo will be provided for 8 weeks. All participants will be divided into 4 groups: (1) the real GJS and real Duolac7S group; (2) the real GJS and placebo Duolac7S group; (3) the placebo GJS and real Duolac7S group; and (4) the placebo GJS and placebo Duolac7S group. The flow of the entire trial is shown in Figure 1.

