The current study has several distinctive features. First, to the best of our knowledge, this will be the first trial to investigate the efficacy of GJS and Duolac7S combination therapy on D-IBS. In spite of the beneficial effects of GJS on IBS in traditional medicine, treatment of IBS by GJS has not been evaluated in clinical trials. No studies have targeted Duolac7S, a mixture of 7 lactic acid bacterial species, as a treatment for D-IBS; however, several studies have suggested that the individual bacterial species in Doulac7S and other probiotics mixtures may improve IBS symptoms. Moreover, GJS and Duolac7S combination therapy has never been the subject of a previous study. Thus, it is expected that the present trial will provide evidence for the effective application of GJS and Duolac7S combination therapy in D-IBS. Second, the participants in the current trial will be grouped into 4 arms. Test groups in this study will be divided into 4 arms in order to identify the efficacy of the combination therapy and to compare each treatment's effect. Ultimately, the combination therapy of GJS and Duolac7S are postulated to generate a synergistic effect resulting in greater improvement of D-IBS symptoms than individual GJS or Duolac7S treatment. Third, we will conduct analyses of intestinal permeability and the composition of intestinal microbiota after administration of GJS with Duolac7S. The urine and stool analysis results could provide evidence for the combination treatment and the possible mechanisms might also be investigated.

Although our study has a relatively small sample size for a pilot study, our trial is considered to have creative and challenging characteristics and is expected to play an important role in providing basic clinical data in the field of herbs and probiotics and developing methodology in IBS studies.

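### The only between-arm efficacy analysis named is a 4-group ANOVA, which does not test whether the combination beats each agent alone

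*Protocol article*

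**What the plan says.** The Hypothesis section of the protocol article states that "GJS combined with Duolac7S will show more beneficial effects on D-IBS symptoms than either GJS or Duolac7S alone". The Discussion says that patients are "divided into 4 arms in order to identify the efficacy of the combination therapy and to compare each treatment's effect", and that the two agents together "are postulated to generate a synergistic effect resulting in greater improvement of D-IBS symptoms than individual GJS or Duolac7S treatment".

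Under Design the arms are listed as "1) the real GJS and real Duolac7S group; (2) the real GJS and placebo Duolac7S group; (3) the placebo GJS and real Duolac7S group", followed by a fourth group that receives both placebos. That is GJS (real or placebo) crossed with Duolac7S (real or placebo), although the article never calls the design factorial.

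Under Statistical analysis the between-arm method is "Comparison between the 4 groups will be performed on the basis of repeated measure ANOVA". The only other efficacy test is a paired t-test against baseline within each group, which compares no arms. No contrast, main effect or interaction is named. The Sample size calculation claims 80% power for the study agents against placebos.

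**The concern.** The hypothesis is directional and has two parts: the combination must beat GJS alone, and it must beat Duolac7S alone. A 4-group comparison has no direction and points at no particular pair of arms. It can be significant because one agent works and the other adds nothing, because all three active arms do equally well, or even because the combination does worse than its components.

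The synergy statement in the Discussion raises a further question. If two effects simply add, the combination beats each agent with no interaction at all. Superiority over each component therefore does not show synergy.

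What is at stake is the trial's main conclusion. With no deciding comparison named, a significant 4-group result could be taken as support for a hypothesis that it does not address, or the pair of arms to report could be picked after the four means are seen.

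**Working it through.** **The plan's own figure.** 12 completers / (1 − 0.20) = 15 per arm, and 15 × 4 = 60. The sample size reproduces. The 80% power cannot be checked, because no effect size, SD or responder rate is given.

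**Inputs.** 12 completers per arm and P < 0.05 come from the Sample size calculation; two-sided testing is assumed. All effect sizes, in SD units, are assumptions. Each patient contributes one normal summary with SD 1, standing in for the between-group part of the repeated-measures ANOVA. Residual df = 4 × (12 − 1) = 44.

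**Formulas.**
- 4-group test: F on 3 and 44 df, with noncentrality λ = 12 × Σ(arm mean − grand mean)².
- One pair of arms: SE = √(2/12) = 0.408 SD.
- Marginal main effect of one agent: SE = √(1/12) = 0.289 SD.
- Interaction: SE = √(4/12) = 0.577 SD, twice that of a main effect.
- Both contrasts significant in the combination's favour: by simulation, because they share the combination arm.

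**The 4-group test when the hypothesis is false.** Arms are in the order combination, GJS, Duolac7S, placebo.

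| Assumed means (SD) | λ | 4-group test significant | Both contrasts succeed |
|---|---|---|---|
| 0.8, 0.8, 0, 0 | 12 × 4 × 0.4² = 7.68 | 59% | about 2% |
| 1, 1, 0, 0 | 12 × 4 × 0.5² = 12 | 80% | about 2% |
| 1.2, 1.2, 1.2, 0 | 12 × (3 × 0.3² + 0.9²) = 12.96 | 84% | about 0.5% |
| 0, 1, 1, 0 | 12 × 4 × 0.5² = 12 | 80% | 0% |

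**When the hypothesis is true.** With additive effects of 0.8 SD each (means 1.6, 0.8, 0.8, 0), λ = 12 × (0.8² + 0.8²) = 15.36. The 4-group test is significant in 90% of trials, but both contrasts succeed in only 32%. The interaction test rejects in 5%, its nominal level, as it should when effects only add.

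**Single-agent aim.** For a GJS effect of 0.8 SD with no interaction, the marginal main effect has power 77% (0.8/0.289 = 2.77). GJS alone against double placebo has 48% (0.8/0.408 = 1.96).

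**Binary outcome.** For illustration, take a 4x2 chi-square test with 12 per arm, Duolac7S inert and an assumed 30% response without GJS. It is significant in about 18%, 38% and 64% of trials when response with GJS is 50%, 60% and 70%. The direction is the same; the size depends on the assumed rates.

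**The case against.** The strongest reply is that the article does not exclude contrasts. It never says omnibus, and a repeated-measures model can carry pairwise or factorial contrasts that a full protocol or analysis plan might list. A reader might infer that the plan forbids them or treats the arms as unrelated; the text supports neither. What remains is that the method it does state does not correspond to the hypothesis it does state, and that mismatch is visible in the article itself.

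A reader might also take 59% to 80% as a false-positive rate. It is not: it is power to detect a real GJS effect. The article nowhere says that a significant 4-group result establishes the hypothesis, so a false claim would follow only if it were read that way. The percentages also rest on assumed effects and a normal outcome, whereas the primary outcomes are weekly yes/no relief and the responder proportion.

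Third, it is tempting to say that factorial margins would give the hypothesis 30 versus 30 patients. They would not. The margins serve the separate aim of comparing each treatment's effect, and they are interpretable only if interaction is small, while the Discussion postulates synergy. The contrasts that decide the hypothesis stay at 15 versus 15.

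Fourth, the Hypothesis section requires no interaction test. Synergy appears only in the Discussion, and interaction depends on scale. With placebo at 20% and each agent at 40%, no interaction means a combination rate of 40 + 40 − 20 = 60% on the risk scale, but 64% on the logit scale.

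Finally, the trial calls itself a pilot. That tempers what it can conclude. It does not remove the need to say which comparison answers the stated hypothesis, particularly beside an 80% power claim.

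**Conclusion.** The point holds as a mismatch between hypothesis and analysis. The named 4-group comparison can be significant when the combination is no better than one agent: 59% to 80% of trials if GJS alone works by an assumed 0.8 to 1.0 SD, with 12 completers per arm and one normal summary per patient. In the same settings the two comparisons that the hypothesis needs would both succeed in about 2%. The qualitative conclusion does not depend on these assumptions; the percentages do, and they should not be carried over to the binary primary outcomes. The synergy wording is a secondary matter that needs an interaction on a stated scale.

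**What to change.** 1. Name two contrasts as the test of the first hypothesis: combination minus GJS alone, and combination minus Duolac7S alone. Claim the hypothesis only if both favour the combination at two-sided 0.05. Because both must succeed, no alpha split is needed.
2. Estimate them from a model with GJS (yes/no), Duolac7S (yes/no) and their product, suited to each outcome: a binary model for the responder outcome, with its scale stated.
3. For the aim of comparing each treatment's effect, report the marginal main effects beside the interaction, with 95% confidence intervals on a stated scale. Say that the margins are interpretable only if interaction is small. Reserve the word synergistic for that interaction.

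The cost is wording: arms, sample size and data collection are unchanged. The price to state openly is that the two contrasts remain 15 versus 15, with about 32% joint power under assumed additive effects of 0.8 SD at 12 completers per arm. The article should also say that its 80% power refers to study agents against placebos and does not cover this hypothesis.
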